# Implementation and effectiveness of evriMED with short messages service (SMS) reminders and tailored feedback compared to standard care on adherence to treatment among tuberculosis patients in Kilimanjaro, Tanzania: proposal for a cluster randomized controlled trial

**DOI:** 10.1186/s13063-019-3483-4

**Published:** 2019-07-12

**Keywords:** Tuberculosis, Adherence, mHealth, Real-time medication monitoring, evriMED, Cluster randomized trial, Resource-limited setting

## Abstract

**Background:**

Adherence to tuberculosis (TB) treatment is challenging because of many factors. The World Health Organization has recommended the use of digital adherence monitoring technologies in its End TB Strategy. However, evidence on improving adherence is limited. EvriMED is a real-time medication-monitoring device which was found to be feasible and acceptable in a few studies in Asia. In Tanzania, however, there may be challenges in implementing evriMED due to stigmatization, network and power access, accuracy, and cost effectiveness, which may have implications for treatment outcome. We propose a pragmatic cluster randomized trial to investigate the effectiveness of evriMED with reminder cues and tailored feedback on adherence to TB treatment in Kilimanjaro, Tanzania.

**Methods/design:**

We will create clusters in Kilimanjaro based on level of health care facility. Clusters will be randomized in an intervention arm, where evriMED will be implemented, or a control arm, where standard practice directly observed treatment will be followed. TB patients in intervention clusters will take their medication from the evriMED pillbox and receive tailored feedback. We will use the ‘Stages of Change’ model, which assumes that a person has to go through the stages of pre-contemplation, contemplation, preparation, action, and evaluation to change behavior for tailored feedback on adherence reports from the device.

**Discussion:**

If the intervention shows a significant effect on adherence and the devices are accepted, accurate, and sustainable, the intervention can be scaled up within the National Tuberculosis Programmes.

**Trial registration:**

Pan African Clinical Trials Registry, PACTR201811755733759. Registered on 8 November 2018.

**Electronic supplementary material:**

The online version of this article (10.1186/s13063-019-3483-4) contains supplementary material, which is available to authorized users.

## Background

Tuberculosis (TB) is among the main communicable diseases causing mortality worldwide, with 10.4 million cases in 2017, of whom 1.7 million died [1]. The World Health Organization (WHO) has set targets in its 2017 ‘END TB Strategy’ for reducing TB deaths by 95% and new cases by 90% by 2035 [2]. However, the END TB Strategy is hampered by the rapidly rising rates of multi-drug-resistant (MDR) TB, with 558,000 cases in 2017 worldwide [1]. Currently, TB treatment is the cornerstone of TB control, but inadequate adherence to treatment is a major factor that leads to treatment failures or development of MDR TB. TB patients have to take four types of pills for 2 months and then two types of pills for another four months; if patients adhere to this regime, they will feel much better within the first two weeks. The number of pills and the six-month duration of therapy causes challenges to TB patients with regard to adherence. Several studies have shown that adherence among TB patients in Sub-Saharan Africa is not reaching adequate levels [3–6]. Specifically, two studies in Tanzania have shown that only 79% of TB patients reached levels of 95% adherence to TB treatment in Kilimanjaro and only 83% reached adequate adherence in Mwanza [7, 8]. Having an estimated TB incidence rate of 269 (range 127–464) per 100,000 population in 2017, Tanzania is among the countries with the highest numbers of TB cases [9]. The estimated mortality rate was 47 (range 21–83) per 100,000 population in 2017 and the proportion of TB cases with MDR TB was 0.9% [9]. Treatment success is not satisfying with rates of 90% in Tanzania in 2017 [9]. The WHO has recommended directly observed treatment (DOT) for many years to improve adherence. However, the implementation of DOT in Sub-Saharan African countries, including Tanzania, is limited, leading to adherence to treatment still being a major challenge [10]. As such, the END TB Strategy recommends to use digital adherence technologies, but with the remark that evidence that such technologies improve adherence is still limited [2].

Several factors have been found to contribute to low levels of adherence which can be summarized into patient characteristics, treatment characteristics, the patient–doctor relationship, and the organization of healthcare services [6, 11–16]. A qualitative study among TB patients in the Kilimanjaro region [11] was one of the first studies in which the relationship between adherence-influencing factors was translated into a (preliminary) model. In this model (Fig. 1), the patient’s intention to adhere to treatment is considered the most important determinant. Adherence-enabling factors include the use of reminder cues such as alarms of mobile phones [11]. According to the model, *health education interventions* are a prerequisite for adequate adherence to treatment. Health education could improve patients’ understanding of the importance of completing treatment and can be delivered through strategies involving mobile devices (Fig. 1, arrow 1) [4, 17, 18]. Reminder cues could facilitate adherence (Fig. 1, arrow 4), particularly when offered in combination with other interventions [19, 20]. According to this model, however, reminder cues alone are unlikely to make a difference in individuals who lack the intention to adhere. Also, conceding to patients’ needs and requests with respect to health care services (i.e., enhancing the ‘adherence-enabling environment’) will help patients to adhere [21–23].

**Fig. 1 Fig1:**
[figure not shown]
Theoretical model of treatment adherence behavior by TB patients [11]

Tailored feedback can target other factors that may influence adherence as determined in the model. The Stages of Change model was previously shown to be a useful model for changing health behavior, including treatment adherence [24–26]. It may provide guidance on the content of tailored feedback to enhance adherence behavior. This model proposes that health behavior change evolves through several stages: pre-contemplation, contemplation, preparation, action, maintenance, and termination. If during feedback sessions it is revealed that a patient’s level of treatment adherence has improved, this may further strengthen the participant’s adherence behavior (positive reinforcement). This may also foster higher self-efficacy (a person’s expectation that he can successfully perform a certain behavior) and internal locus of control (they believe that their own actions determine what happens to a person and not a change of external circumstances). Tailored feedback can be established through extensive counseling using *tailored feedback on individual adherence data.* Of note, such data can be captured through mHealth strategies.

mHealth intervention studies make use of mobile phones for communication with patients. Several innovative mHealth interventions have proven feasible in controlled settings; nevertheless, the evidence on feasibility and effect on adherence in real world settings in Africa is limited [27–30]. Short message service (SMS) seems to be a very promising way to assist TB patients to adhere to treatment as the penetration of simple mobile phones that use SMS for communication is high at over 80% in Tanzania [31]. Previous studies in a variety of medical conditions have shown the feasibility and acceptability of using SMS for adherence reminders in Lesotho and China [32, 33]. Effectiveness has been questioned if SMS is implemented on a large scale and for longer times. Some studies using SMS only for reminding patients have shown limited to no effect on adherence in Cameroon, China, Pakistan, and Uganda [34–37], while others have shown improvements in adherence in Malaysia and China [38, 39]. Most studies mention that SMS might cause privacy concerns, although patients have reported their appreciation of the SMS and feel like someone is taking care of them [32]. Despite varying results, authors have recommended larger studies with interactive communication between patients and health care workers and that studies should be conducted in different settings [29, 33–35, 37–39], especially in low income settings [28].

Real-time medication monitoring (RTMM) devices are a promising innovation that can be used to trigger SMS reminder cues in real time [40, 41]. RTMM works in such a way that an SMS reminder is sent to a patient only if medication is not taken at an agreed time point. Furthermore, it can create adherence reports that can be used to discuss adherence patterns with patients. In one study in Sub-Saharan Africa, RTMM (Wisepill) was shown to be feasible and it was sensitive in detecting non-adherence among MDR TB patients [42]. In Tanzania, Wisepill was considered helpful for improving adherence and was also mentioned to be a good means of storage of medications for TB patients and people living with HIV (PLHIV) [43]. Furthermore, a study in China has shown the feasibility and acceptability of a new RTMM device specifically developed for TB patients called evriMED [44]. EvriMED is different from Wisepill as it is bigger, can contain full blisters of medication, and has a different design for sending data about medication intakes. To our knowledge, no robust clinical trials have studied the efficacy and effectiveness of RTMM in improving adherence among TB patients in Sub-Saharan settings, although several studies have recommended such studies [42, 43, 45–47].

In the resource-limited setting of Kilimanjaro, mHealth may be challenging due to electrical power shortages and low availability of mobile networks. WHO, in its END TB Strategy, has advised the use of digital adherence technologies to improved adherence and specifically evriMED [2]. However, there are concerns about the implementation of evriMED in Tanzania. We believe that the appearance of the device, which is white-colored, has beeping alarm sounds and lights, and is the size of a lunchbox [48], may lead to stigmatization, leading to limited acceptance by TB patients. Furthermore, acceptance by health care providers may be hampered because they will have to use adherence reports for feedback. Also, accuracy is in question as opening of the box does not necessarily mean pill intake. Lastly, RTMM use in real-world settings in Sub-Saharan Africa has not been investigated yet. We therefore propose a pragmatic cluster randomized trial in Kilimanjaro to investigate the effectiveness of EvriMED, which will be used to generate reminder cues and adherence performance reports for tailored feedback.

## Methods/design

### Study area

Kilimanjaro Region has an area of 13,250 km^2^. It has seven districts and the capital is Moshi. In the latest census of 2012, the region had a population of about 1.6 million with a sex ratio of 94 males per 100 females. Seventy-six percent live in rural areas and 38% are aged under 15 years. The number of new TB diagnoses in Kilimanjaro in 2017 was 2681; 1126 (42%) were female. The number of previously treated patients was 54 (2%), with 21 (41%) being female. Of all cases, 263 (10%) were aged under 15 years. In Tanzania, TB patients can choose to use home-based DOT, where they assign someone in their own environment as treatment supporter, or facility-based DOT, where the patient comes to the clinic daily for medication intake [10]. Home-based DOT was chosen by 2574 (96%) patients, while 107 chose facility-based DOT [49]. There was one confirmed MDR case. We have no data on undetected cases. These numbers are based on reported cases to the National Tuberculosis and Leprosy Programme (NTLP) of Tanzania, while national WHO estimates of the number of cases is nearly double that of NTLP [50]. According to NTLP, Kilimanjaro had a treatment success rate of around 92% in 2017 with no difference between men and women [49].

### Design

This will be a pragmatic cluster randomized clinical trial with two arms. We will create 12 clusters in Kilimanjaro based on level of health care facility, numbers of reported TB cases in 2017, and location based on districts. Clusters will be randomized in an intervention arm, where evriMED will be implemented, or a control arm, where standard practice DOT will be followed. TB patients in intervention clusters will take their medication from the evriMED pillbox and receive tailored feedback on adherence during consultation. We will use the Stages of Change model to give this feedback.

### Ethics approval

This trial has been approved by the College Research and Ethics Review Committee (CRERC) of Kilimanjaro Christian Medical University College (KCMUCo) and the National Health Research Ethics Sub-Committee (NatHREC) of the National Medical Research Institute (NIMR) of Tanzania. Furthermore, the regional representatives of the Ministry of Health, the regional medical officer, and of the National Tuberculosis and Leprosy Programme, the Regional Tuberculosis Officer, have given permission to conduct the study.

### Participants

The target population consists of all diagnosed drug-susceptible adult TB patients in Kilimanjaro Region, Tanzania. Inclusion criteria are: diagnosed drug-susceptible TB patients (including smear negative patients); attending care at any of the TB treatment centers in Kilimanjaro Region; aged between 18 and 65 years; living in Kilimanjaro Region; willing to use the evriMED-device; willing to come to the clinic according to standard care; able to read and understand SMS; and able to understand and willing to sign the informed consent document. The following patients are excluded from this study: participating in other trials or previously participated in studies with electronic monitoring devices.

### Intervention

The RTMM device (evriMED1000) is a pillbox containing a SIM card. The evriMED1000 pillbox records and stores medication events (with date and time information) every time the pillbox is opened. The evriMED1000 also sends a heartbeat event every day. The heartbeat event contains device identification and shows the health of the device with technical information on battery status and signal strength. Every day, for the first opening on that day, these data are sent to a central server through the mobile network in near real-time (within 2 min). The first event and all unsent events (heartbeat and medication events) will be sent to the server at this time. If the evriMED1000 is not opened on any day, any unsent (heartbeat and medication) events will be sent at the time of the next heartbeat event.

We will configure an intake period on the server. This is the timeframe in which the medication should be taken. At the start of the intake period, an SMS message will be sent to the mobile number of the participant to remind the participant to take their medication (currently part of standard care). If the medication is not taken within one hour of the intake period, the participant will receive another reminder SMS message. The pillbox can hold enough pills as it has been designed to hold a month’s supply of up to five to ten different prescribed pills.

The intervention comprises two components. One component is the real time intervention consisting of a reminder cue through SMS in case of no intake and the other is the tailored feedback on adherence data. The reminder cues are generated as described above.

#### Attending the nurse; feedback on adherence data

Details of follow-up of patients during clinic visits are displayed in the flowchart (Table 1). After being diagnosed with TB, patients start with a consultation by the physician, which is standard care. Afterwards in the intensive and continuation phase, the participants receive usual care from the DOT nurse. The usual care by DOT nurses will be standardized in order to prevent confounding differences between control and intervention arms. Following standard care, patients in the intervention arm will receive feedback on adherence reports on each visit, which is every 2 weeks for patients in the intensive phase and after every month for patients in the continuation phase for 6 months (see Table 1). We propose a modified version of the Stages of Change model for the feedback. It combines several psychological elements, most notably corrective feedback, but education, goal setting, reinforcement, and improvement of self-efficacy will be implicated as well.

**Table 1 Tab1:** Schedule of enrolment, interventions, and assessments

Visit	Visit 1	Visit 2	Visit 3	Visit 4	Visit 5	Visit 6	Visit 8	Visit 9	Visit 10
Time schedule (intensive and continuation phases)	Day 0	Day 14	Day 28	Day 42	Day 56	Day 84	Day 112	Day 140	Day 168
Provide patient information	C, R								
Oral explanation	C, R								
In- and exclusion form	C, R								
Sign informed consent	C, R								
Enrolment interview	C, R								
Questions session (including self-reported adherence)	C, R	C, R	C, R	C, R	C, R	C, R	C, R	C, R	C, R
Standardized consultation	C, R	C, R	C, R	C, R	C, R	C, R	C, R	C, R	C, R
Explanation on evriMED device	R	R	R	R	R	R	R	R	R
Provide medication	C, R	C, R	C, R	C, R	C, R	C, R	C, R	C, R	C, R
Place medication in evriMED	R	R	R	R	R	R	R	R	R
Pharmacy refill counts		C, R	C, R	C, R	C, R	C, R	C, R	C, R	C, R
Feedback sessions		R	R	R	R	R	R	R	
Evaluation									
Isoniazid urine test		C, R	C, R	C, R	C, R	C, R	C, R	C, R	C, R
Unannounced pill counts		C, R	C, R	C, R	C, R	C, R	C, R	C, R	C, R
Sputum smear test	C, R				C, R			C, R	C, R

*R* RTMM arm, *C* control arm

In the first part of the feedback session, awareness is generated by providing tailored feedback on adherence performance. A graph with medication intake-based data from the pillbox will be shown to participants so they understand where adherence could be improved. In addition, nurses will give basic education on the importance of adherence. After this phase in the session, participants will contemplate on changing their drug taking behavior. Possible pros and cons of changing behavior and barriers to improve adherence will be discussed. Nurses may offer possible solutions, such as “cues” in daily life that are to be coupled with medication intake. The third phase of a feedback session consists of the participant making decisions with respect to their behavior. An adherence goal for the next session will be set by the nurse and participant together (goal setting). The first feedback session (visit 1) will be more extensive than the subsequent feedback sessions depending on whether the patient is in the intensive phase or continuation phase.

### Measurements

#### Main objective

To answer the main objective on effectiveness of evriMED on treatment adherence and outcome, we will measure adherence to treatment in several ways and treatment outcome through sputum smear conversion and relief of symptoms. Adherence will be measured through pharmacy refill counts. This means that, at each visit, we will count the number of leftover medication that the participant brought. As such, they will be instructed to bring their leftover medication always. Furthermore, we will use self-report by asking how many pills were missed since the last visit. Furthermore, we will have adherence data from the evriMED boxes for those participants who are in the treatment arm. These data will show when the pillbox was opened, which is a proxy for medication intake. Based on that, we can count the number of days the box was opened. Adherence will be calculated by ‘Number of days when pills were taken’ divided by ‘Number of days that pills had to be taken’. Sputum smear conversion will be used as treatment outcome and measured according to standard care at month 2, month 5, and month 6 of the treatment course.

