### Sample size calculation and randomization

We calculated that to be able to detect a difference of mean adherence from 79% to 90%, with a power of 80% and significance of 0.05, we would need a sample size of 336 (168 in each arm). As we will use cluster randomization, we used a cluster correlation factor of 0.01. We will need to include 600 patients, 50 in 12 clusters. Considering a drop-out rate of 10%, we anticipate enrolling 660 participants in total. For a period of 8 months, all patients diagnosed with susceptible TB will be asked to participate in our study.

The whole Kilimanjaro Region was divided into 12 clusters based on location in the district, level of health care facility, and number of TB cases in 2017 in each clinic. These clusters were then randomly assigned to provide either standard of care or standard of care and pillbox. A random variable was generated in a dataset containing the clusters. Then, the clusters were sorted using a random variable. The first six clusters were assigned to intervention and the last six to control. Randomization was done using Stata 15.1.

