### Conclusions

If evriMED, used for SMS reminders and tailored feedback during clinic visits, is shown to improve adherence to TB treatment and treatment outcomes, and is acceptable, feasible, and accurate, it could be recommended for standard card among TB patients in Sub-Saharan Africa. Further implementation studies will then be needed to explore factors that may hinder implementation of evriMED if used on a wider scale.

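### Treatment outcome, as worded, gives no unfavourable end-of-treatment result to participants who die, abandon treatment or transfer before month 5

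*Protocol article*

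**What the plan says.** In the protocol article, the Main objective section under Measurements joins two aims, adherence and treatment outcome. It describes the second as "treatment outcome through sputum smear conversion and relief of symptoms" and then fixes it: "Sputum smear conversion will be used as treatment outcome and measured according to standard care at month 2, month 5, and month 6". No time or method of assessment is given for symptoms.

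Table 1 agrees. Its row "Sputum smear test" has entries for both arms at days 0, 56, 140 and 168, all scheduled clinic visits (column positions as read from the extracted table).

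No measure in the article records death, abandonment of treatment or transfer. No sentence says whether a participant without a later smear counts as not converted, is left out, or is handled in another way.

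The programme's own end-of-treatment measure appears only as context. The Study area section reports that "Kilimanjaro had a treatment success rate of around 92% in 2017", citing the national programme. The Conclusions section makes a possible recommendation depend on whether evriMED "is shown to improve adherence to TB treatment and treatment outcomes", and the Discussion likewise expects better treatment outcomes to follow from better adherence.

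**The concern.** Smear conversion and symptom relief can be observed only in someone who is still in contact with care. A participant who leaves before day 56 has no follow-up smear. One who leaves between day 56 and day 140 has a month 2 smear and nothing that describes how treatment ended. These endings are among the worst that treatment can have, and the stated outcome has no category for them.

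This matters more here than in many trials, because reminders and feedback are meant to keep people taking treatment. Being present at months 5 and 6 may therefore itself be an effect of allocation. A comparison of available smears would condition on that post-randomisation event. If the intervention prevented deaths or abandonment, little or none of that benefit would appear in the smear result, and a conclusion about treatment outcomes would rest on a measure that does not see it.

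**Working it through.** **The plan's own figures.** The only numerical planning in the article concerns adherence. For 79% versus 90%, two-sided 0.05 and 80% power, the two-proportion formula is

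n = [1.96 × √(2 × 0.845 × 0.155) + 0.842 × √(0.79 × 0.21 + 0.90 × 0.10)]² / 0.11² = 168.7, so 169 per arm, against the stated 168.

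Clustering: 168 × (1 + 49 × 0.01) / 50 = 5.01 clusters per arm. Adding one gives 6 per arm, so 12 × 50 = 600. Drop-out: 600 × 1.10 = 660. No figure is stated for treatment outcome, so nothing in the sample size changes with this point.

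**Illustration 1: how much of a real difference would be seen.**

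Inputs:
- Control success 92%: the Kilimanjaro figure in the Study area section.
- Intervention success 96%: assumed.
- 300 per arm: 600 / 2 from the sample size section. That all of them can be evaluated by smear is assumed.
- s, the share of unsuccessful patients with no final smear: assumed, and the same in both arms.
- Successful patients all have a converted final smear, and unsuccessful patients with a final smear are not converted: assumed.

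Unsuccessful patients: U = 0.08 × 300 = 24 (control) and 0.04 × 300 = 12 (intervention). Non-conversion among those with a final smear is U(1 − s) / (300 − U·s).

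| s | Control | Intervention | Difference seen |
|---|---|---|---|
| 0 | 24/300 = 8.0% | 12/300 = 4.0% | 4.0 points |
| 50% | 12/288 = 4.2% | 6/294 = 2.0% | 2.1 points |
| 80% | 4.8/280.8 = 1.7% | 2.4/290.4 = 0.8% | 0.9 points |
| 100% | 0/276 = 0% | 0/288 = 0% | 0 points |

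(Differences are taken before rounding.)

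**Illustration 2: when the restriction matters.** Assume 95% conversion among those with a smear in both arms. The comparison of available smears then shows 0 points whatever the losses. If losses count as unsuccessful, the difference is 0.95 × (control loss − intervention loss):

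- 10% vs 10%: 0 points
- 8% vs 4%: 3.8 points
- 10% vs 5%: 4.8 points
- 15% vs 5%: 9.5 points

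So in this illustration the gap in the definition has no effect when loss is equal between arms. It grows with the difference in loss.

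**The case against.** The strongest reply is that the article never says participants without a smear are excluded, and that the handling of missing smears is normally left to an analysis plan or full protocol, neither of which is at hand. The first part stands: a complete-case analysis is something a reader might infer, and the text does not support it. The second part does not dispose of the point. The article itself fixes which outcome is used. A missing-data rule would not ordinarily replace a named outcome or bring in an end-of-treatment result that the article's measurement list does not include.

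Other objections narrow the point:

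- A reader might say that the outcome rests on smears alone. It does not, since relief of symptoms is named as well. That too needs contact with the participant, so the gap remains.
- A reader might say that leavers have no outcome at all. Those who leave after month 2 can have a conversion result at that time. They lack an end-of-treatment result.
- Smears follow standard care, so leaving the study need not mean leaving routine testing. The 10% drop-out allowance therefore cannot be read as the share of missing smears.
- The 92% is background description and not a declared benchmark. It covers a regional case load in which 10% were under 15 years, whereas the trial enrols ages 18 to 65. Smear-negative patients are also eligible, so fewer than 300 per arm would be smear-evaluable.
- Stopping treatment may be reflected in the adherence measure, if its denominator is read to include days after stopping. The article does not settle that.
- The Conclusions sentence is conditional. It still names treatment outcomes as something the trial is to show.

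**Conclusion.** The point holds as a weakness in the stated outcome. Treatment outcome is part of the main objective, and its definition gives no unfavourable end-of-treatment result to participants who die, abandon treatment or transfer before month 5. Under the assumed inputs, a true 4-point difference shrinks to about 2.1, 0.9 or 0 points as the share of unsuccessful patients without a final smear goes from 50% to 80% to 100%. The 96%, the values of s, equal s in both arms and full smear-evaluability are all assumptions. The effect depends on the intervention changing retention, which is plausible but not established.

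A reader might go further and infer that the intervention would be made to look worse. The working shows attenuation, not reversal. Reversal would need s to be sufficiently lower in the intervention arm than in the control arm, and the documents give no figures for that.

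The adherence comparison and the sample size are unaffected. The change should be made, but the trial's main comparison does not depend on it.

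**What to change.** Add the national programme's end-of-treatment result, the source of the success rate in the Study area section, as the treatment outcome for every enrolled participant, analysed by cluster of enrolment. Count death, failure, loss to follow-up and not evaluated as unsuccessful, whether or not the participant stayed with the device or the study visits. Keep smear conversion at months 2, 5 and 6 as a supporting measure, and state how participants without a later smear are classified in it.

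The cost is one register field per participant and a change to the outcome wording. That the trial can obtain this field is an assumption: the Strengths section reports close collaboration with the programme but mentions it in connection with scale-up, not data extraction. Transfers may be coded as not evaluated and would then count as unsuccessful, so results should be reported with and without them. The Trial status section says that recruitment had not started, so on that account the wording could be changed before any outcome data exist.
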